### Inclusion criteria

Histologically proven colorectal adenocarcinoma patients above the age of 18 years within one year of completion of main cancer treatment who are able to provide informed consent.

### Exclusion criteria

CRC patients who have persistent or recurrent disease at the time of the recruitment, are receiving cancer treatment, suffer from hereditary CRC syndrome(s), have known contraindication to PA, are unable to read Chinese, have intakes of red/proceed meat less than five servings per week and refined grains less than two servings daily, or accumulate more than 300 minutes per week of MVPA.

### Participant recruitment

Patients will be identified from the CRC Case Management Programme conducted in each participating hospital. Cancer diagnosis and treatment status will be confirmed by medical record review.

Potentially eligible participants will be mailed an introductory letter containing information about the study, followed by an initial contact (phone or in person at the clinic) by the Cancer Case Manager of each participating hospital. Patients who express their interest will then be approached by the research staff for further screening of eligibility and informed consent if deemed eligible.

### Informed consent

Those who state their interest in taking part will be given any further information they require and, if eligible, invited to the participating hospital to provide informed consent.

### Registration

Data on individuals invited to participate in the trial, whether they consent to be contacted by the research staff, and their eligibility will be kept by the Cancer Case Managers who initially contacted the potential participants. The research staff will also keep a log of any individuals who decline at the trial consent meeting. A computerized case report form will be completed for all consenting individuals. Details of a primary caregiver (if applicable) will also be collected to facilitate participant follow-up. The research staff will use the trial database to enter and store data on all eligible individuals. Recruitment information will also be monitored at regular intervals by comparing this to the numbers being approached and the numbers declining.

### Withdrawal and loss to follow-up

Individuals have the right to withdraw consent for participation in any aspect of this trial at any time. Their medical care will not be affected at any time by declining to participate in or withdrawing from the trial.

The research team will make every effort to minimize the loss to follow-up. If a participant misses one follow-up, we will try to re-arrange with them a session on at least two further occasions. Participants will receive a travel allowance for attending baseline and outcome assessment at the study centre (the University of Hong Kong).

### Trial intervention

#### The intervention groups

“Moving Bright, Eating Smart” is a personalised, multiple-contact intervention programme based on the TPB [13] and the HAPA [22] which guide interventions on health self-regulation that involve motivation, volitional and actional processes for adopting and maintaining health-enhancing behaviours [22,27]. The HAPA addresses the intention-behaviour gap and aims to identify and modify the mechanism of behaviour change (mediators). The objectives/milestones for each stage of change are shown in Table 2.

**Table 2 T2:** Milestones for each HAPA stage of change

**HAPA stage**	**Milestones**
Pre-intentional stage	1. Change in attitude regarding behaviour change
	2. Perceive behavioural health-link
	3. Perceive social pressure for behavioural change from significant others
Intentional stage	1. Intention to modify behaviour
	2. Perceive behavioural control
	3. Develop optimistic belief about ability to deal with barriers
Actional stage	1. Goal setting and review of behavioural goals
	2. Action planning
	3. Self-monitoring of performance
	4. Feedback
	5. Develop coping strategies to deal with barriers
	6. Behaviour maintenance (relapse prevention and recovery)

Abbreviations: HAPA-Health Action Process Approach.

### Physical activity intervention

The PA targets are:

a. General health target of 30 minutes of MVPA 5 days a week (10 MET-hours per week)

b. Cancer outcome target of 60 minutes of MVPA 5 days a week (18–20 MET-hours per week).

During the first six months, participants will be asked to increase PA progressively to achieve the general health target with the aim of progressing towards the cancer outcome target in the next six months. Our previous unpublished research (Phase 0) indicated that the two most preferred modes of PA intervention would be home-based exercise and an incidental active lifestyle.

The PA intervention will consist of:

(1) One face-to-face motivational interview with emphasis on instilling the belief in health and cancer outcome improvement by increasing PA level, goal setting, exploring PA options, exploring perceived facilitators and barriers to PA change and demonstrating the use of a pedometer for progress monitoring;

(2) Fortnightly motivational phone calls for progress monitoring, providing encouragement and reinforcement as well as problem solving;

(3) Monthly HAPA-stage-of-change matched pamphlets by mail providing information, practical tips and suggested task to consolidate PA change;

(4) Quarterly newsletters by mail for experience sharing among participants;

(5) Quarterly group meetings for promoting social support, demonstrating various PA options and facilitating discussion on barriers to PA change.

All PA participants will be given a pedometer and a monthly PA log as means of monitoring changes in PA level.

### Dietary intervention

The dietary targets are:

(a) Less than five servings of red/processed meat weekly; less than two servings of which will be processed meat;

(b) Two servings of refined grains daily.

During the first six months, participants will be asked to gradually reduce red/processed meat first, followed by refined grains. They will be encouraged to replace red/processed meat with other protein sources and refined grains with wholegrain. In order to establish and enhance perceived self-efficacy to maximize the probability of desired behavioural change, a staggered approach will be adopted, focusing on reduction of red/processed meat first. Strategies to reduce refined grain intake will be initiated within one month after a participant becomes an “actor” of reduced red/processed meat. During the next six months, participants will be expected to progress towards the dietary targets as stated above.

Similar to the PA intervention, the dietary intervention will consist of:

(1) Two face-to-face motivational interviews, one for red/processed meat and another for refined grains;

(2) Fortnightly motivational phone calls;

(3) Monthly HAPA-stage-of-change matched information pamphlets by mail;

(4) Quarterly newsletters by mail;

(5) Quarterly group meeting.

All participants in the dietary group will be given a food diary with monthly dietary logs for monitoring changes in the intakes of red/processed meat and refined grains. A set of eating utensils will also be given to facilitate portion size estimation.

### PA and dietary intervention

This group will receive, where possible, an integrated version of both intervention components. This integrated approach is necessary to avoid intervention overload (participant fatigue) in this particular group.

For all subjects in the intervention groups, the exact content and the pace of the intervention delivered will depend on the participants’ extant PA and dietary pattern, medical co-morbidities, HAPA stage and individual preferences.

### The usual care (control) group

Similar to those in the intervention groups, the usual care participants will be mailed, at regular intervals, five pamphlets containing general advice encouraging a healthy lifestyle, including eating a wide variety of food, eating more fruit and vegetable, increasing physical activity level, maintaining a normal body weight, quitting smoking and avoiding alcohol abuse. The above mentioned information is widely available in the public domains (websites of the World Health Organization and the Department of Health in Hong Kong).

Maintaining contact with these participants from the baseline assessment to the various outcome assessments is done to minimize loss to follow-up. Furthermore, this practice would ensure that all participants receive some lifestyle advice that at the moment is given on an ad hoc basis. We anticipate that the effect of these pamphlets alone would be small.

Figure 1 illustrates the participant pathway throughout the trial.

**Figure 1 F1:**
[figure not shown]
Participant flow chart.

### Serious adverse events and adverse events

No serious adverse events (SAE) are anticipated. However, if any SAE occurs, this will be reported to the Institutional Review Boards and will also be drawn to the immediate attention of the clinical collaborators of the participating departments.

Participants receiving the dietary intervention will be monitored to prevent specific nutrient deficiency including inadequate caloric and protein intakes and iron-deficiency anaemia due to inadequate red meat intake. Participants receiving the PA intervention will be monitored for PA-associated injury.

### Statistical considerations

#### Randomisation

A randomisation schedule will be generated by block randomisation with stratification by study centre and stoma status. The block size will be decided and securely kept by a randomiser who will not be involved in subject recruitment. The randomisation will be managed centrally by the randomiser. When an eligible patient consents to participate in the study, the recruiter will obtain the treatment code from a centralised access restricted randomisation system.

### Sample size

In the control arm, we do not expect that a sizable percentage of participants will achieve the behavioural targets. Nevertheless, we conservatively assume that 10% of them will reach the targeted levels at one year, which results in a larger required sample size to detect the intervention effects. Although we are optimistic about the intervention effect, based on our clinical experience, we consider that a 10-20% improvement in the intervention arm over the usual care would be regarded as minimally significant for promoting the use of the intervention. Hence, we assume an effect size of 15%. To achieve 80% power with a 5% false positive error rate to detect this effect size by a chi-square test, we need 50 subjects per cell and thus 200 patients in total. Expecting a 10% dropout rate, we will need to recruit 224 patients for the study. The sample size should be sufficient when the improvement is larger than expected.

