### Primary outcome

To evaluate the acceptability and feasibility of two behaviour interventions for CRC survivors intended to improve cancer outcome. These interventions are designed to:

1. Increase PA levels to improve general health and cancer outcome;

2. Decrease consumption of a Western-pattern diet.

The PA target for improving general health is 30 minutes of moderate-to-vigorous intensity PA (MVPA) five days a week (equivalent to 10 MET-hours per week). The PA target for improving cancer outcome is 60 minutes of MVPA five days a week (equivalent to 18–20 MET-hours per week).

The dietary targets are to limit weekly red or processed meat intake to <5 servings and to limit daily refined grain intake to two servings.

The primary outcome measure will be whether the PA or dietary targets are met at the end of the 12-month intervention.

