**Primary outcome**		
PA target – general health	Accelerometer	0 M, 6 M, 12 M, 18 M, 24 M
PA target – cancer outcome	Accelerometer	0 M, 6 M, 12 M, 18 M, 24 M
Dietary target – red/processed meat	FFQ [30]	0 M, 6 M, 12 M, 18 M, 24 M
Dietary target – refined grain	FFQ [30]	0 M, 6 M, 12 M, 18 M, 24 M

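### Eligibility lets in patients who may already meet the general-health activity target or a single-food target, so the 10% control rate and the 80% power are not supported for those targets

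*Protocol article*

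**What the plan says.** **Targets.** Under Primary outcome, "The PA target for improving general health is 30 minutes of moderate-to-vigorous intensity PA (MVPA) five days a week", which is 5 × 30 = 150 minutes a week. The cancer-outcome target is 60 minutes on five days, or 300 minutes a week. The dietary targets are fewer than five weekly servings of red or processed meat and a limit of two daily servings of refined grains. Table 1 gives each its own primary row, including "PA target – general health". Attainment is judged at 12 months, with no condition on status at entry.

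**Eligibility.** Under Exclusion criteria, the dietary exclusion covers patients who "have intakes of red/proceed meat less than five servings per week and refined grains less than two servings daily". The activity exclusion is a separate condition that acts only at the upper end: "or accumulate more than 300 minutes per week of MVPA".

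**Sample size.** For the control arm, "we conservatively assume that 10% of them will reach the targeted levels at one year". The section justifies the word *conservatively* by saying that this assumption enlarges the required sample. The effect is set in absolute terms, as a percentage-point difference: "Hence, we assume an effect size of 15". Power, error rate and test come next: "To achieve 80% power with a 5% false positive error rate to detect this effect size by a chi-square test". The size derived from them is stated as follows: "we need 50 subjects per cell and thus 200 patients in total".

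**Analysis.** The main analysis is a logistic regression on all randomised patients, with missing values counted as target not reached. The adjustments named are recruitment site and stoma status. Baseline status on the target is not among them, although all four targets are measured at 0 months.

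**The concern.** The eligibility cut-offs match some primary targets and not others. A patient at 200 minutes a week is eligible and above the weekly total of the general-health target. A patient eating three servings of meat a week and four servings of refined grains a day is eligible and already within the meat target; the reverse case applies to grains. For these three Table 1 rows, the control rate at 12 months includes patients who started at target and stayed there, as well as those who reached it during the year.

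For an effect fixed in percentage points, assuming 10% is cautious only if the true rate is 10% or lower. A moderately higher rate increases the variance and lowers power. Patients already at target also have less room to gain, which can shrink the overall difference. The trial is meant to inform a Phase 3 design, and the Discussion argues that the moderate activity target is important to evaluate. A non-significant result on that target could be read as failure of the intervention when the comparison was underpowered.

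**Working it through.** **Inputs.** From Sample size: control 10%, effect 15 points, power 80%, α 5% (sidedness not stated; two-sided reproduces the figure), 50 per cell. In the 2×2 factorial each intervention is tested on a margin of 2 × 50 = 100 against 100.

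**1. The plan's own figure.** With pooled variance under the null, n per margin is

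n = [1.960·√(2p̄(1−p̄)) + 0.842·√(p₁(1−p₁) + p₂(1−p₂))]² / (p₂−p₁)²

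For p₁ = 0.10, p₂ = 0.25, p̄ = 0.175: [1.960·√0.28875 + 0.842·√0.2775]² / 0.0225 = 99.5. That is 100 per margin, 50 per cell, 200 in total, and power at 100 per margin is 0.802. Allowing for 10% dropout gives 200/0.9 = 223 after rounding up, against 224 stated. The calculation reproduces.

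**2. Which primary rows can be met at entry?**

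| Table 1 row | Kept out at entry? |
|---|---|
| Activity, general health (150 min/week) | No: 150–300 min/week is eligible |
| Activity, cancer outcome (300 min/week) | Yes, except exactly 300 min |
| Red/processed meat (<5/week) | No: eligible if grains are not below 2/day |
| Refined grain (2/day) | No: eligible if meat is not below 5/week |
| *Both dietary targets together (not a Table 1 row)* | Yes, except <5 meat with exactly 2 grain servings |

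**3. Power when the control rate is higher.** The documents give no baseline attainment, so the control rate c is an assumed range. The effect stays at the plan's 15 points, with 100 per margin:

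power = Φ{[0.15·√100 − 1.960·√(2p̄(1−p̄))] / √(p₁(1−p₁) + p₂(1−p₂))}

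Example, c = 0.20: (1.5 − 1.960·√0.39875)/√0.3875 = 0.42, giving 0.663.

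| Control | Intervention | Power | Evaluable total for 80% |
|---|---|---|---|
| 10% | 25% | 0.802 | 200 |
| 15% | 30% | 0.722 | 242 |
| 20% | 35% | 0.663 | 276 |
| 30% | 45% | 0.592 | 326 |
| 40% | 55% | 0.566 | 346 |

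**4. Power when only patients not at target gain.** Let a share b enter at target and a fraction r of them remain there in both arms, with the rest reaching it at 10% against 25%. Then control = b·r + 0.10(1−b) and intervention = b·r + 0.25(1−b). Both b and r are assumptions. Example, b = 0.20, r = 0.80: control 0.16 + 0.08 = 24%, intervention 0.16 + 0.20 = 36%, power 0.456.

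| b | r = 1.0 | r = 0.8 | r = 0.6 |
|---|---|---|---|
| 10% | 0.589 | 0.613 | 0.640 |
| 20% | 0.432 | 0.456 | 0.490 |
| 30% | 0.323 | 0.338 | 0.365 |

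**5. What 10% would require.** With no new attainers at all and r = 0.8, a control rate of 10% needs 0.8·b ≤ 0.10, so b ≤ 12.5%. The exclusion criteria do not ensure this and the sample-size section does not show it.

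**The case against.** **10% may still be right.** There is no baseline distribution in the article. The rate could be 10% or less if few entrants are at target or if many relapse. The activity target is worded as five days a week and measured by accelerometer, so a weekly total of 150 minutes does not by itself establish attainment. The Dietary intervention section adds a limit of fewer than two processed-meat servings, which could narrow the meat target. Missing values count as failures. All of this stands. A reader might infer that 10% cannot hold, or that the 80% claim is false; the documents support neither.

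**The dietary endpoint may be joint.** The Discussion treats the meat and grain levels together as a single dietary target. On that reading the *and* in the exclusion fits the endpoint and the single-food concern largely falls away. Table 1's separate rows leave the matter open.

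**The activity targets are nested.** A reader might infer that 10% for both activity targets means nobody can lie between 150 and 299 minutes. That follows only if both rates are exactly 10%. Read as a ceiling, 10% or less on the easier target implies 10% or less on the harder one, with no contradiction.

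**Patients at target can still benefit.** Table 2 lists relapse prevention among the intervention milestones, so it is wrong to say that they cannot be helped. Step 4 sets retention equal in both arms; better retention under intervention would raise its powers.

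**The loss depends on the effect scale.** 10% against 25% is an odds ratio of (0.25/0.75)/(0.10/0.90) = 3. Holding that ratio constant, power rises to 0.942 at 20% control and 0.968 at 30%. This is correct, but the plan states its effect in absolute points, derived from a minimally important improvement of 10–20%.

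**This is a feasibility trial, described in a condensed article.** Confidence intervals and the magnitude-of-change outcomes mean that a null binary result is not the only evidence. That limits the consequence. It does not remove the mismatch, because the eligibility rules, the single rate and the word *conservatively* are all stated in the article.

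**Conclusion.** The concern holds in limited form. Eligibility and endpoint do not match for the general-health activity target and, if the dietary endpoints are separate, for the meat and grain targets. For these the 10% control rate is unsupported and not shown to be conservative, so 80% power is not assured. On the plan's absolute 15-point scale, power is 72% at a 15% control rate, 66% at 20% and 59% at 30%. If only patients not at target gain, an illustrative case gives 46% (20% enter at target, 80% of those stay there in both arms). These control rates, b and r are assumptions, because the documents give no baseline attainment.

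Eligibility does not undermine the 10% rate for the 300-minute activity target or for both dietary targets together, apart from the boundary cases in step 2.

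**What to change.** 1. **Sample size.** State that the 10% against 25% calculation and its 80% power apply to the endpoints that eligibility leaves essentially unmet at entry: 300 minutes a week of activity, and both dietary targets jointly. For the general-health activity and single-food targets, give power over control rates of about 10–40%, as in step 3. Delete *conservatively*.
2. **Main analysis.** Add the baseline value or baseline attainment of the corresponding target, already collected at 0 months, to the primary logistic model. Where almost nobody is at target on entry, the baseline value is the more usable form. Add a supporting analysis among patients not at target at baseline.
3. **Primary outcome.** State whether the dietary primary endpoint is joint or separate, so that it can be read consistently with the *and* in the exclusion criterion.

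The four primary rows in Table 1 need not be demoted. The cost is wording, one covariate and one supporting analysis, with no extra patients or measurements. The downside is a less favourable stated power for some targets.

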### Analysis

#### Main analysis

Efficacy of the dietary and PA interventions in helping patients to reach the corresponding behavioural target will be assessed by logistic regression analysis. Model adequacy will be examined by the Hosmer-Lemeshow goodness of fit test. The analysis will be performed on two analysis sets, full and per-protocol, to examine the sensitivity of results due to non-compliance. The full analysis set includes all patients as randomised. Patients with missing values will be taken as if they did not reach the targeted level. The per-protocol set includes all patients who complied with the intervention and have no missing values. Conclusions will be made from the results derived from the full analysis set, which is consistent with the intention-to-treat principle. All analysis will be adjusted for recruitment sites and stoma status.

Analysis of secondary outcomes will be performed by mixed-effects analysis to account for extra covariance from repeated measurements taken from a participant.

A 95% confidence interval will accompany all effect estimates and a 5% level of significance will be used in all significance tests.

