### Treatment period and follow up

Dietary and PA interventions will be delivered over a 12 month period and participants will be followed up for a further 12 months.

Baseline assessment will be conducted at the University of Hong Kong. All baseline measures will be made prior to group allocation. An interim outcome assessment will be performed six months after randomization. Outcome/follow-up assessments will be made at 12, 18 and 24 months after randomization. Staff responsible for outcome assessment will not deliver the intervention. All outcome assessments will be subject to a strict protocol with researchers blinded to group allocation.

All participants (including the usual care group) will be given written, publicly-available general advice that encourages healthy lifestyles.

Participants in the PA intervention group will have one face-to-face intervention contact at the beginning followed by fortnightly telephone contacts for 12 months. They will also receive 12 stage-based information pamphlets and four newsletters by mail and will attend four group meetings during the 12-month intervention period.

Participants in the dietary intervention group will have two face-to-face intervention contacts during the first four months and fortnightly telephone contacts throughout the 12 months. They will also receive 12 stage-based information pamphlets and four newsletters by mail and will attend four group meetings during the 12-month intervention period.

The interventions will be delivered by trained research staff and the research team members.

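### The primary logistic model leaves out the baseline level of the behaviour being tested; the analysis is valid and meets its stated power, but it gives up precision that data already collected would supply

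*Protocol article*

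**What the plan says.** The Primary outcome section defines a binary endpoint: "The primary outcome measure will be whether the PA or dietary targets are met at the end of the 12-month intervention". Under Main analysis, the effect of each intervention on helping patients "reach the corresponding behavioural target will be assessed by logistic regression analysis", and the covariates are then stated: "All analysis will be adjusted for recruitment sites and stoma status". These are the two factors used in the allocation, which is by "block randomisation with stratification by study centre and stoma status".

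Table 1 schedules the accelerometer (both physical activity targets) and the FFQ (both dietary targets) at "0 M, 6 M, 12 M, 18 M, 24 M". The section on treatment period and follow-up adds: "All baseline measures will be made prior to group allocation". A pre-randomisation value of each outcome variable, from the same instrument, is therefore planned for every participant.

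The exclusion criteria leave room for spread at entry. On activity they remove only those who "accumulate more than 300 minutes per week of MVPA". On diet, read literally, they remove only those who "have intakes of red/proceed meat less than five servings per week and refined grains less than two servings daily", that is, people below both limits.

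**The concern.** The endpoint is a level at 12 months and not a change, so where a participant starts is likely to bear on whether the target is met. Someone entering with 150 to 300 minutes of moderate-to-vigorous activity a week is already at the weekly total of the general health target (30 minutes × 5 days = 150). Someone below one dietary limit but not the other is eligible and already meets one of the two dietary targets. Neither the stratification nor the model takes account of this.

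Two things are at stake. The primary test uses less information than the trial will hold. And in the one trial that is run, a chance difference between arms in starting behaviour stays in the effect estimate. The estimate matters beyond its p-value, because the Discussion says the observed magnitude of behaviour change will inform the design of a phase 3 trial.

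**Working it through.** **1. The plan's own figure.** Inputs from the Sample size section: 10% at target under control, a 15-point improvement (so 25%), 5% error rate (taken as two-sided), 80% power, chi-square test. With pooled variance and no continuity correction, the mean proportion is 0.175 and

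n = [1.960 × √(2 × 0.175 × 0.825) + 0.842 × √(0.10 × 0.90 + 0.25 × 0.75)]² / 0.15²
= (1.053 + 0.443)² / 0.0225 ≈ 99.5, so 100 per factorial margin.

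That is 50 per cell and 200 in total, as stated, with power 80.2%. For dropout, 4 × (50 / 0.9 rounded up to 56) = 224, also as stated. The calculation rests on an unadjusted test, so nothing in it depends on the baseline covariate.

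**2. Power with and without the baseline value.** The article gives no correlation between baseline and 12-month behaviour, so 0.3 to 0.7 is an assumption. Model: 2×2 factorial, N = 200; normal baseline B; latent outcome ρB + √(1 − ρ²)·e; target met above a cut-off that gives 10% and 25% in the two arms of the tested factor. No effect of the other factor, site or stoma was assumed (three sites, 20% with a stoma). The logistic model contained both factors, site and stoma, with or without B, and used a likelihood-ratio test at 5%, with 4,000 runs per row.

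| Assumed correlation | Without baseline | With baseline | Gain (points) |
|---|---|---|---|
| 0 | 80.8% | 80.9% | 0.1 |
| 0.3 | 82.3% | 84.0% | 1.7 |
| 0.5 | 81.4% | 86.5% | 5.1 |
| 0.7 | 82.2% | 92.3% | 10.0 |

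A separate simulation of the same design point gave 81% to 82%, 83% to 87% and 80% to 91% at correlations 0.3, 0.5 and 0.7. Simulation error therefore leaves the gain at about 1–2, 4–6 and 10–11 points. With 224 recruited and a 10% dropout counted as failure, as the full analysis set requires, the figures are 82.0% to 82.5%, 81.1% to 86.6% and 80.5% to 89.8%.

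With no treatment effect and correlation 0.5, the rejection rate was 5.8% without and 5.9% with the covariate, so adjustment does no harm to the error rate.

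**3. What a chance imbalance does.** With 100 per margin, the difference in mean standardised baseline has SD √(2/100) = 0.141. Under the same latent model, a unit shift in baseline changes the target rate by about ρ × φ(cut-off), where φ is the normal density: 0.1755 at the 10% cut-off and 0.3178 at the 25% cut-off, mean 0.2466. A 1-SD imbalance therefore moves the risk difference by ρ × 0.2466 × 0.141:

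- ρ = 0.3: 1.0 points
- ρ = 0.5: 1.7 points (1.75, or about 1.8, by simulation)
- ρ = 0.7: 2.4 points

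A 2-SD imbalance moves it by about 2.1, 3.5 and 4.9 points (simulated), against the planned 15.

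**The case against.** The strongest reply is that nothing in the article is wrong. The model adjusts for exactly the factors used in stratification, randomisation protects the error rate, and the planned power is met without the covariate. All of that stands. It makes this an improvement to a valid plan and not the repair of a broken one.

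A second reply is that the covariate sentence does not exclude further covariates, and that an analysis plan, not shown, may add them. This has some weight, but the sentence covers all analyses and names a set. A plan that added baseline behaviour would be changing what the article states.

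Third, the gain is uncertain. No baseline data are given, and at a correlation of 0.3 the gain is slight. This also stands, and is why a range is shown.

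Fourth, adjustment has a price. About 35 events are expected (10 + 25), a dietary model may need two extra terms, and the odds ratio becomes conditional on baseline. These costs are small, and reporting a standardised risk difference meets the last one.

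Two stronger readings are tempting and are not supported:

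- **That the primary test is underpowered.** One can obtain 60–64% power without the covariate and 65–76% with it (correlations 0.5 to 0.7) by assuming log-normal activity with median 90 minutes, log-SD 0.9, truncation at 300 and a 0.4 SD shift. None of those inputs is in the article, the scenario covers only the 150-minute target, and it is not the protocol's design point.
- **That imbalance passes straight into the result, or biases it.** If 21% were at target at entry, the imbalance in that status would have SD √(2 × 0.21 × 0.79 / 100) = 5.8 points, but this cannot be set directly against the 15-point effect. Under that same assumed distribution, being at target at entry raises the 12-month rate by about 25 to 39 points (correlations 0.5 to 0.7), so only 0.0576 × 0.25 to 0.0576 × 0.39, or about 1.4 to 2.2 points, carries through. That variation is already in the confidence interval and averages out over repeated randomisation. Nor does the 21% figure apply to the 300-minute target, since people above 300 minutes are excluded.

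**Conclusion.** The point holds as a loss of efficiency. The stated covariate set omits a pre-allocation measure of the outcome variable that the trial will collect from everyone and does not balance by design. Depending on a correlation the article does not give, including it would add from about 1 to about 10 points of power to a test that already reaches 80%. It would also remove chance shifts of about 1.0 to 2.4 points per SD of baseline imbalance from the estimated difference.

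These sizes rest on the protocol's 10% versus 25%, 100 per margin, a latent-normal outcome and correlations of 0.3 to 0.7. The dietary and activity targets were not modelled separately. The validity of the test and the sample size are not in question. The change is worth making, and should be fixed in advance, because a covariate added after an imbalance is seen would look data-driven.

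**What to change.** Extend the covariate sentence under Main analysis, for example: *Every model will include recruitment site, stoma status and the continuous baseline value of the variable from which the outcome is derived.* For both activity targets this is baseline accelerometer activity; for each dietary target, the corresponding baseline FFQ servings. Use the continuous value and not baseline target status, which is nearly constant for the 300-minute target because of the exclusion.

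Report a standardised (marginal) risk difference with its 95% confidence interval beside the conditional odds ratio, so that the result can be compared with the 15-point design effect.

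The cost is one or two sentences and one or two model parameters. The sample size and the assessment schedule do not change.
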